### Participants’ recruitment

All of the 210 patients treated by hemodialysis or online-hemodiafiltration in the participating centers will be screened for the presence of criteria for PEW. The principal investigators will review the existing patients’ database for serum albumin, serum prealbumin, C-reactive protein (CRP) levels*,* body mass index (BMI) and the presence of weight loss according to the PEW criteria. Potential subjects will have additional tests (measure of lean body mass index by bio-impedance and a 3-day dietary record by a qualified dietician in order to evaluate their protein and energy intake). Patients fulfilling inclusion/exclusion criteria and having signed an informed consent for the study participation will undergo randomization generated by a computer program. We expect to recruit approximately fifty HD patients for this study.

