### Intervention

All the patients will continue their usual dialysis procedure (HD or HDF). No modifications of dialysis modality or prescriptions are allowed except for adaptation of dry weight using clinical criteria.

Both patients in the control and exercise groups will receive dietary counseling by a trained dietician. The prescription of oral nutritional complements or intradialytic parenteral nutrition will be adapted to patient needs according to the dietary record in order to attain goals set by the EBP guidelines for gender energy intake 30–40 kcal/kg of ideal weight/day, and protein intake > 1.1 g/kg of ideal weight/day.

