### Statistical analysis

The sample size was calculated considering the number of patients who are no longer in a state of protein energy wasting after 6 months of exercise training compared to the control group. For a significance level of 0.05 and 80% power, it was estimated that 22 participants would be required in each group.

Results will be expressed as minimum to maximum or percentage of change, as applicable, and mean ± standard deviation. To test the effects of Group (Exercise *versus* Control) on all outcome measures, univariate two-way analyses of variance (ANOVAs), with the Group (×2) as between-subjects factor and Time (t_0_, t_+2_, t_+4_ and t_+6_) as the within subject factor, will be carried out for each aforesaid dependent variable. For each analysis, the level of significance was p < 0.05. Newman-Keuls comparisons will be used for post-hoc tests following significant effects. If the sphericity assumption in ANOVA is violated (Mauchly’s test), corrected tests of significance will be used [45,46]. In that case, the paired t-tests with corrected alpha level will be used as post-hoc comparisons. All the statistical analyses will be conducted using a SPSS software package.

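### For the continuous outcomes, the post-hoc rules suit a between-arm question poorly: paired t-tests compare visits only, and Newman-Keuls lacks strong family-error control with four or more means

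*Protocol article*

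**What the plan says.** The Statistical analysis section of the protocol article sets out to test the effect of Group on every outcome. It uses a two-way ANOVA with Group (two levels, between patients) and Time (t0, t+2, t+4, t+6, within patients), and "For each analysis, the level of significance was p < 0.05".

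Two follow-up rules are then fixed:

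- By default, "Newman-Keuls comparisons will be used for post-hoc tests following significant effects".
- If Mauchly's test shows that sphericity is violated, the F tests are corrected and the follow-up changes: "In that case, the paired t-tests with corrected alpha level will be used as post-hoc comparisons".

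The section does not say which effect (Group, Time or Group by Time) opens the follow-up tests, which set of means they compare, or how alpha is corrected. The size of the trial is given there too: "it was estimated that 22 participants would be required in each group".

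The Intervention section adds a relevant fact: "Both patients in the control and exercise groups will receive dietary counseling by a trained dietician". Nutritional support in both arms is adjusted towards the same intake goals.

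**The concern.** The arms are independent randomised groups. A paired t-test needs two measurements on the same patient, so it can only compare visits. Once Mauchly's test rejects, the plan therefore names no follow-up that compares exercise with control. Correcting alpha does not help, because the fault is the contrast and not the threshold.

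The section leaves a reader with one p-value per arm, and the natural misuse is to read a significant change in one arm only as a treatment effect. Because both arms receive nutritional support, change in both is plausible, and that is the setting in which this pattern misleads.

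On the other branch, Newman-Keuls can compare the arms at a visit, but it does not hold the family error rate at 5% for every configuration of four or more means. Which kind of follow-up an outcome receives also depends on a pre-test of its own data, so outcomes within the same trial may be followed up with different kinds of contrast.

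At stake is the statement of when, and in which direction, the arms differ on the continuous outcomes. The primary outcome is a count of patients, to which these follow-up tests do not naturally apply.

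**Working it through.** **Inputs from the protocol article.** Alpha 0.05 per analysis; 22 per arm; two arms and four visits, so 2 × 4 = 8 cells.

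**Assumptions not in the article.** An equal true change in both arms of 0.4-0.6 SD from t0 to t+6; correlation between visits 0.3-0.8; alpha corrected to 0.05/6 = 0.0083 (six pairs of four visits); follow-up opened by a significant Time or Group by Time F test; independent cell means in the Newman-Keuls runs.

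**The plan's own figure.** The 22 per arm cannot be reproduced, because the article gives no response rates. Two-sided and without continuity correction it fits, for example, 10% v 48% or 20% v 61%. It is neither confirmed nor refuted, and serves here only as n.

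**1. Paired t-tests with no F test first.** Let p be the power of a paired t-test (non-central t, 21 df, non-centrality d√22, with d in SDs of the change). With the same true change in both arms, the chance that exactly one arm is significant is 2p(1 − p).

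| d | p at 0.05 | 2p(1 − p) | p at 0.05/6 | 2p(1 − p) |
|---|---|---|---|---|
| 0.4 | 0.43 | 0.49 | 0.18 | 0.30 |
| 0.5 | 0.61 | 0.48 | 0.31 | 0.43 |
| 0.6 | 0.77 | 0.36 | 0.48 | 0.50 |

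(The products use unrounded p.) The maximum is about 0.50 at either alpha; a stricter threshold only moves the change at which it occurs, from d = 0.45 to d = 0.60.

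**2. The same pattern with an F test first.** The plan says that follow-up comes after significant effects, so the ungated figures are not the plan's figures. The ANOVA was simulated (4,000 runs per setting, 22 per arm, compound symmetry, equal linear change in both arms), with t0 v t+6 tested by paired t at 0.05/6 only after a significant Time or Group by Time effect. Here the change is in SDs of a single measurement.

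| Correlation | Change (SD) | Significant in exactly one arm | Group by Time F rejects |
|---|---|---|---|
| 0.3 | 0.4 | 17.6% | 5.2% |
| 0.3 | 0.6 | 43.8% | 5.1% |
| 0.6 | 0.4 | 34.4% | 5.2% |
| 0.6 | 0.6 | 47.6% | 5.2% |
| 0.8 | 0.4 | 49.2% | 4.9% |
| 0.8 | 0.6 | 13.5% | 4.6% |

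The range is about 14-49%. By symmetry half of these cases favour exercise, so about 7-25%. The last row is low because the change is then 0.6/√(2 × 0.2) = 0.95 SDs of the change, and both arms are usually significant.

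If only a significant Group by Time effect opens the tests, the misleading pattern cannot occur more often than that F test rejects: about 5%.

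**3. Newman-Keuls.** When the means form separated pairs, equal within each pair, every pair is tested at the two-mean level. With m independent pairs the family error is 1 − 0.95^m. Simulation used 20,000 runs, n = 22 per cell:

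| Configuration | Formula | Simulated |
|---|---|---|
| 4 means, all equal | 5% | 4.9% |
| 8 means, all equal | 5% | 4.9% |
| 4 means, two separated pairs | 1 − 0.95² = 9.75% | 9.6% |
| 8 means, four separated pairs | 1 − 0.95⁴ = 18.5% | 18.8% |

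With two means, Newman-Keuls is the t-test (critical value 2.018 at 42 df for both).

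**The case against.** The strongest reply is that the between-arm test is the ANOVA, not the follow-up. Group has two levels and needs no post-hoc test; sphericity does not affect the Group main effect; and the F tests are corrected when sphericity fails. This stands. A reader might infer that the plan cannot support any between-arm conclusion on these outcomes, but the document does not bear that out: the Group by Time F test held its level in the simulation, where sphericity was true, and nothing in the section says that the conclusion rests on the post-hoc tests. The F tests do not replace the follow-up, however. The Group main effect averages over all four visits including the pre-treatment one, and the three-degree-of-freedom interaction does not say where or in which direction the arms differ.

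Second, paired comparisons of visits are an ordinary follow-up to a Time effect, alpha is corrected, and the article nowhere plans to read significance in one arm only as a treatment effect. This also stands. The misreading is a risk that the rule leaves open, not a stated analysis.

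Third, the ungated 36-50% (alpha 0.05) and 30-50% (alpha/6) ignore the requirement of a significant effect. A reader might take them as the plan's false-positive rate; they are not.

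Fourth, it would be too strong to say simply that Newman-Keuls fails to hold 5%. It holds under the complete null and with two or three means, and it can compare arms at a visit. The four-visit figure concerns Time, not the arms, and both inflated figures are worst cases with well-separated, independent pairs.

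Finally, an article may leave the list of contrasts and the alpha correction to a fuller document, so their absence is not the complaint. What remains is that the two rules actually stated are poorly chosen for the stated purpose.

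**Conclusion.** The point holds in a limited form, for the follow-up tests on continuous, mainly secondary, outcomes. When sphericity is rejected, the only named follow-up cannot compare the arms. Whether that misleads often depends on a gate that the article does not specify: about 14-49% if a Time effect is enough to open the tests, about 5% if Group by Time is required. The first range rests on the assumed 0.4-0.6 SD changes, correlations of 0.3-0.8 and alpha/6. It was simulated under compound symmetry, although this branch applies when sphericity is rejected, so it shows the order of magnitude only. When sphericity is not rejected, Newman-Keuls can let the family error rise to about 10% over four visit means or about 19% over eight cells under partial nulls. The planned F tests remain a between-arm comparison, and the point does not bear on the analysis of the binary primary outcome.

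**What to change.** Replace both post-hoc sentences in the Statistical analysis section with the following:

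- For each continuous outcome, the between-arm conclusion rests on the Group by Time test or on a single prespecified contrast: exercise minus control in change from baseline to t+6, taken from the planned ANOVA framework or an equivalent model.
- The corresponding contrasts at t+2 and t+4 are supportive, with Holm adjustment.
- Within-arm changes are reported descriptively with confidence intervals, and no statement about the arms is drawn from them.

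The choice of follow-up then no longer depends on Mauchly's test. The cost is two rewritten sentences and slightly stricter post-hoc thresholds. No new model, data or patients are needed.

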## Discussion

To our knowledge, this is the first trial investigating the impact of intradialytic exercise combined with an individualized nutritional support on protein energy wasting. It is also the first trial to investigate the influence of exercise on postural balance, which is of special interest for fundamental and clinical purposes (i.e., the important issue of physical condition in dialysis patients). An improved postural balance signifies a decreased incidence of falls and fractures in this high-risk population [47]. The main forces of this trial will be the randomized design and the individualized management of “real life” patients suffering from PEW. It can be argued that the nutritional support will not be the same in all patients as some will have only nutritional counseling and others ONC and a few IDPN. However, according to the literature the different nutrition methods have equivalent efficacy and the prescription of the type of nutritional support will follow actual guidelines. If this current clinical trial can highlight the expected effects of exercise to reverse PEW, at least for a part, it would be a strong argument for implementing an exercise program in this high-risk population and even in the whole dialysis population in order to prevent the occurrence of PEW.
